Small community-based programs have reported some success in modifying surrogate markers for diabetes through lifestyle intervention. The Greater Green Triangle Diabetes Prevention Project in Australia [12] and the Good Ageing in Lahti Region Lifestyle Implementation Trial in Finland [13] confirmed that short-term lifestyle modification programs can reduce risk factors for diabetes in primary care settings.

The current challenge is to translate this evidence into cost-effective large scale community-wide programs. There is increasing acknowledgement that the best way to do this is through studies which have an explicit focus on generalisation and feasibility and which report information on contextual variables such as representativeness, reach, implementation and adaption, costs and other outcomes important to policy makers [14]. Thus the current study employs a design which will not only provide data on intervention effectiveness, but also will examine contextual factors through process evaluation central to what has been called by some the 'science of delivery' [15].

The overall aim of this study is to assess the effectiveness of a community-based lifestyle modification program on modifiable risk factors for type 2 diabetes. Additional aims include assessing the feasibility of delivering the program in a primary health care setting; identifying determinants of the interventions which are associated with and predict a beneficial outcome; and the costs and cost-effectiveness of the program.

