### Intervention - Lifestyle Modification Program

The five aims of the lifestyle modifications are:

1. At least 30 min/day of moderate to vigorous intensity physical activity, including aerobic exercise 3 or more days/week plus strength training at least twice/week (210 min/week total structured exercise)

2. Reduction in the intake of energy from total fat to less than 30%

3. Reduction in the intake of energy from saturated fat to less than 10%

4. Fibre intake of at least 15 g/1000 kcal

5. Achievement of a 5% reduction in body weight at 12 months.

In addition to the 210 min/week structured exercise goal, participants are encouraged to increase incidental physical activity in ways which would enhance both cardiovascular and musculoskeletal fitness.

These five goals are entirely concordant with the Finnish DPS (5), which was one of the most successful diabetes prevention trials. The physical activity goal, which has been modified slightly from the Finnish DPS is based on a review of the physical activity prescriptions utilised in relation to outcomes achieved in all of the successful trials of diabetes prevention (5,6,7,10,11), considerations of cost and feasibility in this translational setting, as well as other literature regarding modality, volume, and intensity of exercise required to improve metabolic risk and body composition in similar cohorts. Both the Finnish DPS and the US DPP included resistance training (strength training) in their supervised exercise sessions and is explicitly specified within the physical activity goal of the SDPP. Resistance training is an anabolic form of exercise, differing substantially from aerobic exercise in its ability to induce muscle hypertrophy and associated metabolic and functional changes [17,18]. It improves insulin sensitivity, glucose homeostasis, blood pressure, dyslipidaemia, markers of inflammation and catabolism, and visceral obesity, thus addressing the key metabolic abnormalities in adults at high risk of type 2 diabetes [19,20]. Importantly, resistance training (but not aerobic exercise) attenuates or prevents the loss of lean tissue (muscle and bone) accompanying weight loss diets such as those prescribed in this study [21].

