### Outcome measures and evaluation plan

The evaluation plan has three components:

1. Impact evaluation measures changes at 12 months in the key outcomes known to be associated with reduced diabetes incidence: weight loss; increase in moderate to vigorous physical activity (including both aerobic and strengthening activities); increase in dietary fibre consumption; decrease in fat consumption and decrease in saturated fat intake. Program and participant factors which predict these outcomes are assessed.

2. Process evaluation measures program reach, fidelity, satisfaction and knowledge of program delivery by staff, satisfaction of consumers, and identifies facilitators and barriers associated with program implementation and delivery.

3. Economic evaluation involves health system and individual perspectives and estimates implementation costs, costs per outcome and cost-effectiveness.

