#### Statistical methods

Analysis at 12 months will determine the extent that program goals were achieved, through overall and sub-group analysis. Primary outcomes which will be reported include weight loss (and 5% weight loss goal achievement), physical activity levels (in minutes per week of overall intentional activity, and sessions per week of strength training) and PASE scores, dietary measures (total energy/day, estimated fibre intake (gm/1,000 kcal), total fat intake (gm/day), fat as a proportion of total energy intake and saturated fat as a proportion of daily energy intake), and proportions of the cohort achieving 1,2,3,4, or all 5 goals. Logistic regression analysis will be used to examine factors associated with the achievement of program goals. Separate models will examine predictors of 5% weight loss, achievement of 210 min/day of physical activity, and achievement of dietary goals.

Missing data due to either refusal to respond to selected questions or withdrawal from the program before the endpoint will be dealt with by imputing values for the discrepant self-reports using data from "similar" participants or using last observation carried forward (LOCF) techniques when appropriate.

A minimal sample size of 1,000 completed participants with baseline and 12 month data will provide 90% power to detect small differences in primary outcomes effects at the 5% level of confidence for the whole group. Specifically, we will be able to detect:

• 5% weight loss

• increase of 2.5 g of fibre/1,000 kcal

• 3.4% reduction of fat intake as a percentage of total energy

• 2.7% reduction of saturated fat intake as a percentage of total fat intake

• 11.7 min/wk of increased physical activity.

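### The evaluation plan asks what predicts the 12-month changes, but the only predictor models named are of yes/no goal achievement, and four of the five goals can be met at entry

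*Protocol article*

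**What the plan says.** In the protocol article, the section Outcome measures and evaluation plan sets the impact question: "Impact evaluation measures changes at 12 months in the key outcomes known to be associated with reduced diabetes incidence". It lists weight loss, more activity, more fibre, less fat and less saturated fat, and continues: "Program and participant factors which predict these outcomes are assessed". The Background makes the search for predictors an additional study aim: "identifying determinants of the interventions which are associated with and predict a beneficial outcome".

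The Statistical methods section then names the models: "Logistic regression analysis will be used to examine factors associated with the achievement of program goals", and "Separate models will examine predictors of 5% weight loss, achievement of 210 min/day of physical activity, and achievement of dietary goals". It lists the continuous measures for reporting, overall and by sub-group, but names no regression for them. It mentions neither adjustment for baseline nor restriction to people below goal at entry.

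The goals are set out under Intervention - Lifestyle Modification Program. The weight goal is a change: "Achievement of a 5% reduction in body weight at 12 months". The others are set as levels, for example "Fibre intake of at least 15 g/1000 kcal" and, for total fat, "Reduction in the intake of energy from total fat to less than 30" per cent. The activity goal is a daily and weekly amount of exercise, and the saturated fat goal is a share of energy.

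**The concern.** The plan asks one question and names a model for a related but different one. What predicts change over 12 months is not the same as what predicts being on the right side of a threshold at 12 months.

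Two things follow. First, where the goal is a level, a participant who meets it at entry and does not change can count as a success. A factor that merely marks better diet or more activity before enrolment will then be associated with attainment and may be read as a determinant of programme success. Secondly, a yes/no outcome carries less information than the measurement behind it, so real predictors are more likely to be missed.

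At stake is the additional aim of identifying who benefits and why. The 12-month effect estimates themselves are not affected.

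**Working it through.** **The plan's own figure.** The document gives no sample size or power for the predictor models. Its one power statement (1,000 completers, 90% power, 5% level) concerns whole-group change. It cannot be reproduced because no standard deviation is given. Read as a two-sided paired comparison, it corresponds to a standardised change of (1.960 + 1.282)/√1000 = 0.1025. Nothing below depends on that figure, but the 1,000 completers are used as the sample size.

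**Which goals can be met at entry.**

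| Goal | Type | Can be met at baseline? |
|---|---|---|
| 5% weight loss | change from baseline | no |
| Physical activity | level | yes |
| Fibre | level | yes |
| Total fat | level, worded as a reduction to below a threshold | yes, depending on coding |
| Saturated fat | as total fat | yes, depending on coding |

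The exclusions under Participants and recruitment concern diabetes, hypoglycaemic and weight-loss medication, and contraindication to exercise. None concerns diet or activity level at entry.

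**Information lost by dichotomising.** Let p be the share at goal, c = Φ⁻¹(1 − p), and φ the standard normal density. For a normal outcome and a small predictor effect, the efficiency of the yes/no outcome relative to the same outcome kept continuous is

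E = φ(c)² / [p(1 − p)].

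Example at p = 0.30: c = 0.524, φ(c) = 0.348, so E = 0.121/0.21 = 0.576. The values of p are assumptions. By symmetry, p and 1 − p give the same E.

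The last column takes a predictor that splits 1,000 people 50:50, with a difference of 2 × (1.960 + 1.282)/√1000 = 0.205 SD. That difference has 90% power on the continuous scale. At p = 0.30 it becomes 33.7% against 26.5% at goal.

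| Assumed p | E | Information lost | Equivalent n out of 1,000 | Power, yes/no outcome |
|---|---|---|---|---|
| 50% | 0.637 | 36% | 637 | 73% |
| 40% | 0.622 | 38% | 622 | 72% |
| 30% | 0.576 | 42% | 576 | 69% |
| 20% | 0.490 | 51% | 490 | 62% |
| 10% | 0.342 | 66% | 342 | 47% |

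**How many attainers might have been at goal already.** The document gives no inputs for this, so it is an illustration only. Take baseline and 12-month values as bivariate normal with equal variances, correlation 0.4 to 0.6, and a mean shift m of 0.2 to 0.4 SD towards the goal. With p0 at goal at baseline and c0 = Φ⁻¹(1 − p0), the share at goal at 12 months is 1 − Φ(c0 − m). For p0 = 20% and m = 0.4, that is 1 − Φ(0.842 − 0.4) = 32.9%. Dividing the joint probability of being at goal at both times by the 12-month share gives:

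| Assumed share at goal at baseline | Share of 12-month attainers already at goal |
|---|---|
| 10% | 22.4% to 34.6% |
| 20% | 33.4% to 45.3% |
| 30% | 42.6% to 53.5% |
| 40% | 51.1% to 60.7% |

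**Why a baseline-adjusted linear model answers the change question.** If the 12-month value is Y12 = a + bX + gY0, then Y12 − Y0 = a + bX + (g − 1)Y0. The coefficient b of predictor X is the same whether the outcome is the 12-month value or the change.

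**The case against.** The strongest reply is that goal attainment is a question the article asks in its own right. The Impact Evaluation section wants to know whether individuals and the group reach the goals, and Statistical methods lists 5% weight-loss achievement and the number of goals met among the primary outcomes. The Background speaks only of a beneficial outcome. Logistic regression suits that question. This stands, and it is why the goal models should be kept. A reader might infer that they are wrong or should be demoted; the documents do not support that.

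A second reply is that covariate lists and supplementary models are usually left to an analysis plan, and none is shown here. This stands in part. The article does not say that continuous outcomes will go unmodelled or that baseline values will be left out, so nobody should infer a decision to that effect. But it does make a choice by naming the model and its dependent variables, and that choice does not match the outcomes in its own evaluation plan.

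A third reply is that the problem of people already at goal is easily overstated. It cannot touch the weight model. For the two fat goals it depends on coding: the Intervention section words them as reductions to below a threshold, whereas the Abstract speaks of limiting intake. How someone below the threshold at entry is counted is not stated. This stands as a limit on the point.

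Finally, the study follows a single active arm. Baseline-adjusted models will show what predicts change among participants, not what modifies the programme's effect. That is true of either model and is no reason to prefer the unadjusted one.

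**Conclusion.** The point holds as a modest improvement to the plan. The evaluation plan asks for predictors of change, and the named models address yes/no attainment only. For activity, fibre and, subject to coding, the two fat goals, those models can credit people who were already at goal unless baseline is taken into account.

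Under normality and small effects, the loss of information is at least 36% and reaches 66% at 10% attainment. Neither condition is shown for weekly activity minutes or three-day food records. A reader might want one headline figure, such as 40%. That would require assuming that about 30% to 40% (or 60% to 70%) reach the goal, and the document gives no attainment rate. The 22% to 61% of attainers already at goal likewise rests wholly on assumed inputs and shows only that the share need not be small.

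**What to change.** - Alongside the logistic goal models, add a linear regression for each of the five measures (weight, activity, fibre, total fat and saturated fat as shares of energy). Regress the 12-month value on the candidate predictors, adjusted for the baseline value of that measure.
- In the activity and dietary goal models, include the baseline value as a covariate, or restrict the model to people below goal at entry. State how someone below a fat threshold at entry is counted. The weight-loss goal model does not need this change.
- Separately, reconcile the activity goal that defines one of the binary endpoints. Statistical methods gives 210 min per day, whereas the Abstract and the Intervention section give 210 min per week.

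Baseline and 12-month values are already to be collected, so the cost is a little more analysis. The downside is a second set of coefficients, in kilograms, grams, percentage points or minutes, to report beside the odds ratios. Restricting to people below goal would also shrink the sample for those models, which including the baseline value as a covariate avoids.

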**Methods/Design:**

The Sydney Diabetes Prevention Program (SDPP) is a translational study which will be conducted in 1,550 participants aged 50-65 years (including 100 indigenous people aged 18 years and older) at high risk of future development of diabetes. Participants will be identified through a screening and recruitment program delivered through primary care and will be offered a community-based lifestyle modification intervention. The intervention comprises an initial individual session and three group sessions based on behaviour change principles and focuses on five goals: 5% weight loss, 210 min/week physical activity (aerobic and strength training exercise), limit dietary fat and saturated fat to less than 30% and 10% of energy intake respectively, and at least 15 g/1000 kcal dietary fibre. This is followed by 3-monthly contact with participants to review progress and offer ongoing lifestyle advice for 12 months. The effectiveness and costs of the program on diabetes-related risk factors will be evaluated. Main outcomes include changes in weight, physical activity, and dietary changes (fat, saturated fat and fibre intake). Secondary outcomes include changes in waist circumference, fasting plasma glucose, blood pressure, lipids, quality of life, psychological well being, medication use and health service utilization.

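### The physical-activity predictor model states its cut-off as 210 minutes per day, while the programme goal is 210 minutes per week

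*Protocol article*

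**What the plan says.** The goal is stated in three places outside the statistical section, each time per week:

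- Abstract, Methods/Design: "210 min/week physical activity (aerobic and strength training exercise".
- Intervention - Lifestyle Modification Program, first aim: "At least 30 min/day of moderate to vigorous intensity physical activity", with aerobic and strength components, summarised in the same aim as "210 min/week total structured exercise".
- The same section, in the paragraph on incidental activity: "In addition to the 210 min/week structured exercise goal".

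Statistical methods lists activity among the primary outcomes in "minutes per week of overall intentional activity, and sessions per week of strength training", together with PASE scores, and also lists the proportions of the cohort meeting one, two, three, four or all five goals. It then says: "Logistic regression analysis will be used to examine factors associated with the achievement of program goals". The next sentence names the separate models. One is for 5% weight loss, one for "achievement of 210 min/day of physical activity", and the rest for the dietary goals.

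**The concern.** The number 210 is the same throughout, but in the model definition the unit is the day instead of the week. A binary cut-off goes straight into analysis code. If the sentence were programmed as it stands, the variable called goal achievement would measure something other than the goal, and the factors found to be associated with it would be predictors of a much higher activity level.

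The same section also counts how many of the five goals each participant meets. With the literal cut-off, a participant at 210 minutes per week could meet the activity goal in that count and be a non-achiever in the predictor model.

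**Working it through.** **Inputs, all from the protocol article**

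- Daily rate in the goal: 30 min/day (intervention section, first aim).
- Weekly total in the goal: 210 min/week (abstract; intervention section, twice).
- Cut-off in the predictor model: 210 min/day (Statistical methods).
- Unit of the activity outcome: minutes per week (Statistical methods).
- Detectable change in activity: 11.7 min/wk (Statistical methods).

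**Step 1: reproduce the goal.** Weekly total = daily rate × 7 = 30 × 7 = 210 min/week. The stated goal is reproduced exactly, so its daily and weekly forms agree.

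**Step 2: put the model's cut-off on the same scale.** 210 min/day × 7 = 1,470 min/week. In hours this is 210 / 60 = 3.5 hours every day, or 1,470 / 60 = 24.5 hours per week.

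**Step 3: compare.** 1,470 / 210 = 7.0. The literal cut-off is seven times the goal.

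**Step 4: could 210 min/day be a deliberate, separate threshold?** The sentence introducing the models says that they concern achievement of the programme goals, and no place in the article sets a goal of 210 minutes per day. The activity outcome and the detectable change in the same section are both weekly. Nothing supports the daily unit.

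**Step 5: what depends on the cut-off?** The continuous outcomes (minutes per week, strength sessions per week, PASE score) do not use it. Nor does the detectable change of 11.7 min/wk, which is stated in weekly minutes. The effect is confined to the activity predictor model and to its agreement with the goal count.

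**The case against.** The strongest reply is that no careful analyst would be misled. The models are said to concern the programme goals, the goal is weekly wherever it is set out, and the same section measures activity per week. On that reading the daily unit is a misprint and the intended analysis is sound. This stands as an account of what was probably meant, and it keeps the point small. It does not make the sentence right: the error is in the definition of an analysis outcome, and would give a wrong variable if followed.

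Three stronger readings are tempting, and the article does not support them.

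- A reader might infer that almost nobody would reach the cut-off and that the model could not be fitted. That is plausible at 3.5 hours a day, but the article gives no distribution of activity and no expected proportion of achievers. It remains an assumption, and the number of achievers could lie anywhere from none to enough for a stable model.
- A reader might infer that the model scores minutes alone and ignores the strength component ("strength training at least twice/week (210 min/week total structured exercise"). The phrase in Statistical methods is a short label in a list of models, not a full scoring rule. The abstract uses a similarly short label for the same goal. Detailed scoring of a composite goal is commonly left to the full protocol or analysis plan, which is not shown.
- A reader might infer that a main conclusion of the study turns on this threshold. No decision rule rests on it. Identifying determinants of a beneficial outcome is an additional aim in the Background; the overall aim is effectiveness on modifiable risk factors.

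**Conclusion.** The statement is wrong as written and contradicts the rest of the article. The factor of seven is exact and needs no assumption beyond a seven-day week. That it takes effect only if the text is followed literally is a judgement, resting on the consistency of every other mention, that the daily unit is a slip.

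The mismatch with the goal count is certain for the literal reading only. Once the unit is corrected no difference between the two can be shown, because the article does not say how the count scores activity. Overall this is a small correction to a secondary predictor analysis.

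**What to change.** In Statistical methods, change the unit of the activity cut-off from day to week, so that the model's outcome is 210 min/week. Add a reference to the physical-activity goal as defined in the first aim of the intervention section, and state that the goal count uses the same definition.

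The unit correction costs one word, and the cross-reference a clause or a sentence. Neither changes the sample size or the continuous outcomes. If the components of the goal are to be scored, strength sessions per week are already a listed outcome. Aerobic days per week and minutes by intensity are not listed, so the sponsor should confirm that the instruments supply them before assuming that no further data are needed.

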### Participants and recruitment

The Divisions of General Practice have recruited over 75 practices and 150 general practitioners (GPs) to participate in the study. This was done through expression of interest by letter and fax, information sessions and site visits. The main pre-requisite for inclusion was the practice having a computerised patient record system.

People aged 50-65 years (18 years and older in the indigenous subgroup) without known diabetes attending study general practices are approached to participate. A variety of methods are used to identify potential participants including opportunistic recruitment when the person attends the general practitioner for a routine consultation, using the practice's computer database to identify people in the target age range and sending a letter suggesting they attend for risk assessment, and local media advertising of the program.

Risk is assessed using the AUSDRISK tool, a questionnaire developed in Australia [16]. The questions focus on demographic and diabetes risk factors and include an objective assessment of waist circumference performed by trained research staff. The maximum AUSDRISK score is 38 and a score of ≥ 15 is considered high risk. A score of 15-19 is associated with a 1 in 7 chance and a score of ≥ 20 with a 1 in 3 chance of developing diabetes over the next 5 years [16]. A score of ≥ 12 is considered high risk in the indigenous subgroup.

A person with a risk score of ≥ 15 is required to undergo investigations to exclude prevalent diabetes. This initially involves measurement of capillary blood glucose in the general practitioner's surgery, followed by measurement of fasting plasma glucose and possibly an oral glucose tolerance test.

Study exclusion criteria include new or previously diagnosed diabetes, taking a hypoglycaemic medication in the past month, use of prescribed weight loss medication or a medical contraindication to participation in a physical activity program. Participants enter the study after written consent is obtained, eligibility criteria have been met and clearance is received from their general practitioner.

The study plans to recruit 1,550 high risk people into the lifestyle intervention program. Among these 100 will be Arabic-speaking, 100 will be Chinese-speaking and 100 will be indigenous people.

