**Figure 1 F1:**
[figure not shown]
**Overview of the program and data collection points for evaluation**.

High risk individuals agreeing to participate in the lifestyle modification program complete an initial computer-assisted telephone interview (CATI) survey. This survey includes socio-economic and demographic information, physical activity habits, quality of life, and self-efficacy, as well as recent health service utilisation and current medication use. Participants are then scheduled to attend an individual consultation with a lifestyle officer. At this consultation, the lifestyle officers measure height, weight and waist circumference using calibrated stadiometers, scales and tape measures, following a standardized anthropometric protocol as specified by the International Society for the Advancement of Kinanthropometry (ISAK) [25]. The individual consultation includes a general discussion about diabetes risk and prevention, an overview of the program, and uses motivational interviewing techniques to assist participants to set goals and develop tools to self-monitor. Following this session, arrangements are made for participants to attend three two-hour group programs held over a six to eight week period. Lifestyle officers conduct these group sessions of approximately 10 people, which cover theoretical, behavioural and practical aspects of diet and physical activity. The overall program motto is: "Eat better and move more". Those who are not able to or do not want to attend a group program are offered the option of three individual health coaching sessions by telephone, covering the same material. The intervention delivered to indigenous participants will be slightly modified to take account of cultural issues.

Follow up telephone calls are made by the lifestyle officers to each participant at 3, 6 and 9 months to enquire about progress, assist with behaviour change and offer participants additional support as required.

In addition, participants are provided with details of local community-based lifestyle programs which have been evaluated by the research staff and found to be consistent with the goals of the SDPP. Participants have the option of enrolling in such programs as one way to assist in achieving the SDPP physical activity and dietary goals.

At 12 months the CATI survey is repeated and participants undergo an individual assessment with the lifestyle officer and their general practitioner.

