#### Impact Evaluation

Outcomes are assessed at baseline and 12 months by research staff, using a combination of in-person assessment and CATI questionnaires. Physical activity is assessed using the Physical Activity Scale for the Elderly (PASE), which has established reliability and validity [26]. Dietary intake (including total fat, saturated fat and fibre) is assessed by a self-completed 3-day non-weighed food record, which is analysed using Foodworks [27].

Weight, height, waist circumference and blood pressure are measured using standard methods. Blood is collected for measurement of fasting plasma glucose and lipids. Additional questions on socio-demographic characteristics, concomitant diseases and medications, smoking, alcohol, social support, self-efficacy for lifestyle change, and quality of life are asked at the baseline and 12 month CATI surveys.

Analyses of these data will determine whether the program goals are achieved by individuals, by the group as a whole and differentially by sub-groups (e.g. GP Division and gender). In addition, these data will be used to model the projected impact of the program beyond the 12-month intervention period.

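### With outcomes described only at baseline and 12 months, LOCF for withdrawals means baseline carried forward, which distorts mean change, goal counts and predictor models; donor imputation, if done once, also understates standard errors

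*Protocol article*

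**What the plan says.** The Statistical methods section of the protocol article gives one rule for two kinds of missing data: refusal of individual questions, and withdrawal before 12 months. The rule has two branches. One is "imputing values for the discrepant self-reports using data from" participants regarded as similar. The other is "using last observation carried forward (LOCF) techniques when appropriate". The section does not define similarity or say when LOCF is appropriate.

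The Impact Evaluation section sets the measurement times: "Outcomes are assessed at baseline and 12 months by research staff". Between these, the text accompanying Figure 1 describes only support contacts: "Follow up telephone calls are made by the lifestyle officers to each participant at 3, 6 and 9 months to enquire about progress". It describes no outcome measurement at those calls.

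On numbers, Participants and recruitment states: "The study plans to recruit 1,550 high risk people into the lifestyle intervention program". The power statement rests on "A minimal sample size of 1,000 completed participants with baseline and 12 month data". No dropout rate is given.

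**The concern.** LOCF is usually offered where there are interim visits to carry forward from. Here the text describes none, so for a withdrawal the only earlier value is baseline. LOCF then amounts to assuming that someone who had part of the program did not change at all. Four results follow:

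- The mean change is pulled towards zero, or flattered if withdrawals in fact got worse.
- The fat, saturated fat, fibre and activity goals are absolute thresholds, so a withdrawal who met one at baseline is counted as an achiever.
- The weight goal is a 5% reduction, so every withdrawal is counted as a failure.
- In the logistic models of goal achievement, whatever predicts withdrawal will appear to predict failure to lose weight.

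The reported proportions meeting one to five goals would mix these distortions, which run in opposite directions. The article describes a single cohort with no comparison arm, so a between-group contrast cannot offset any of this.

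Donor imputation raises a separate issue. If each missing value is filled once and then analysed as if observed, the analysis claims the precision of the full cohort without having its information.

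**Working it through.** **Inputs.** Planned recruitment N = 1,550 (Participants and recruitment). Minimum completers 1,000 (Statistical methods). Two outcome times (Impact Evaluation). The SD of change, s, is not stated, so results are given as ratios or in units of s. The actual missing fraction p is not stated, so a range is used.

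**The plan's own figure.** With n = 1,000, a two-sided 5% level (sidedness is not stated) and 90% power, the detectable change is (1.960 + 1.282)/√1000 = 0.103 s. The stated 90% power cannot be checked without an SD. It refers to completers, so it does not depend on the imputation rule.

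**Implied ceiling on loss.** (1,550 − 1,000)/1,550 = 550/1,550 = 35.5%.

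**LOCF and the mean.** Let completers change by δ on average and withdrawals by kδ.

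- True cohort mean: δ(1 − p + pk).
- LOCF gives δ(1 − p), a relative bias of −pk/(1 − p + pk).
- Filling from completers gives δ, a relative bias of p(1 − k)/(1 − p + pk).

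The values of k are assumptions:

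| What withdrawals do | Method | p = 10% | p = 20% | p = 35.5% |
|---|---|---|---|---|
| Same change as completers (k = 1) | LOCF | −10% | −20% | −35% |
| | Donor | 0% | 0% | 0% |
| Half the change (k = 0.5) | LOCF | −5% | −11% | −22% |
| | Donor | +5% | +11% | +22% |
| Worsen by a quarter of δ (k = −0.25) | LOCF | +3% | +7% | +16% |
| | Donor | +14% | +33% | +80% |

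The row k = 1 is the case of data missing completely at random. A simulation (N = 1,550, 1,000 observed, 3,000 replicates) agreed with the 35.5% column.

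**LOCF and the goals.** Let A be the proportion of completers who meet a goal at 12 months, and B the proportion of withdrawals who met it at baseline.

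- Absolute goals: LOCF reports (1 − p)A + pB.
- 5% weight loss: B is zero by construction, so LOCF reports (1 − p)A, that is 0.90A, 0.80A or 0.645A at the three values of p.

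**Donor imputation and the standard error.** Assume one random donor per missing value, data missing completely at random, and the filled data analysed as observed.

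- Naive variance: s²/N.
- True variance: s²(1/r + m/N²), with r observed and m missing.
- Squared ratio: 1/(1 − p) + p.
- Coverage: 2Φ(1.96/ratio) − 1.

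| p | 1/(1 − p) + p | True SE / naive SE | 95% CI coverage |
|---|---|---|---|
| 10% | 1.111 + 0.100 = 1.211 | 1.10 | about 92-93% |
| 20% | 1.250 + 0.200 = 1.450 | 1.20 | about 90% |
| 35.5% | 1.550 + 0.355 = 1.905 | 1.38 | about 84% |

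At the ceiling, the naive SE is s/√1550 = 0.0254 s, the completers-only SE is s/√1000 = 0.0316 s, and the true SE of the donor estimate is √0.001229 s = 0.0351 s. Type I error is about 16% instead of 5%.

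**LOCF and the standard error.** LOCF does not share this fault. In the simulation with no true change and data missing completely at random, it rejected 5.5% of the time, as did the completers-only analysis. Its naive SE was about 1.0 to 1.17 times the SE of its own estimate. LOCF's fault is bias.

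**The case against.** Several stronger readings are tempting, and the text does not support them.

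- **That about 35% will be missing.** The 1,000 is a minimum for power, and no dropout rate is stated. The 35.5% is a ceiling implied by two figures, which is why the results are shown over a range.
- **That the cohort's weight loss could be reported as 5.0% or 3.2%, depending on the rule chosen.** If completers lost 5.0% (an assumption), LOCF at the ceiling would give 5.0% × 1,000/1,550 = 3.2%, and donor values would give 5.0%. But the donor branch is worded for self-reports, and weight is measured by staff on scales. Read literally, LOCF is the only rule named for weight. An open choice between the rules is clearest for self-reported diet and activity.
- **That the stated rule as a whole both biases effects and understates standard errors.** The two harms belong mainly to different methods: bias to LOCF, and understated error to single donor imputation. With data missing completely at random, the donor method is unbiased.
- **That imputation is stated to be single.** It is not. Drawing from similar participants is also compatible with multiple imputation by matching, so the SE and coverage figures are conditional.

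Two further points deserve weight. Counting withdrawals as not reaching the weight goal is often conservative, and can be defended in a study of real-world delivery. That defence does not reach goals already met at baseline, mean change when withdrawals worsen, or the predictor models. Also, Figure 1 is not available here, so the two time points rest on the text alone.

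It can also be said that a condensed article leaves such detail to an analysis plan. That is fair for the definition of similarity, the variance method and the list of covariates. It does not cover LOCF, which the article itself names for withdrawals.

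**Conclusion.** The concern stands in this limited form. On the measurement schedule as described, LOCF for a withdrawal is baseline carried forward. If data are missing completely at random, it shrinks the mean change by the missing fraction: 10%, 20%, or 35% at the implied ceiling. If withdrawals worsen, it overstates the benefit. It treats the weight goal and the absolute goals inconsistently, and it confuses withdrawal with failure in the logistic models. These conclusions follow from the stated method and do not depend on an SD.

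The precision finding is conditional. If donor values are drawn once and analysed as observed, the true SE is about 1.10, 1.20 and 1.38 times the naive SE, with coverage of about 92-93%, 90% and 84%, at 10%, 20% and 35.5% missing. With lower attrition both effects become small, but the article sets no tighter limit on attrition.

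**What to change.** Name one primary method for missing 12-month outcomes: multiple imputation combined by Rubin's rules, or an equivalent likelihood-based model. Include the baseline value of the outcome and covariates the study already collects, such as age, sex, risk score, Division and session attendance. Derive goal achievement from the imputed values, and use the same imputations for the logistic models, so that carried-forward values do not enter them.

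Keep baseline carried forward (withdrawal means no change; weight goal not achieved) only as a named sensitivity analysis. Because the primary method assumes data are missing at random given the covariates, add a delta-adjusted analysis in which withdrawals do worse than imputed by a stated range. Remove the open wording about when LOCF applies. If a separate analysis plan exists, the two texts should agree.

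The cost is revised wording, modest programming and somewhat wider confidence intervals, which reflect the information actually available. No new data collection is needed.
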